## **A: SPECIFIC AIMS**

Diabetes Mellitus affects approximately 24 million adults in the United States (NIH 2008). African Americans (AA) with Type 2 diabetes (T2DM) have higher prevalence of diabetes, poorer metabolic control (i.e. poorer blood glucose, blood pressure, and lipid control), and greater risk for complications and death compared to White Americans (NIH 2008). Behavioral economics research has identified several decision-making patterns that contribute to poor adherence to medical regimens. Delay discounting represents the extent to which consequences or outcomes decrease in their effectiveness to control behavior the longer the consequences or outcomes are delayed (Reynolds 2006). Therefore, adults with diabetes who prefer smaller, immediate benefits (e.g. eating preferred foods or not being inconvenienced by exercising or taking medications) over larger, delayed benefits (e.g. better metabolic control, reduced risk of complications, or reduced risk of dying), are less likely to make healthy lifestyle decisions. Using financial incentives to promote medical adherence and healthy behaviors is consistent with behavioral economic theory and findings (Sutherland 2008). We propose a pilot randomized controlled study to test the efficacy of financial incentives augmented telephone-delivered diabetes education and skills training intervention compared to usual care in improving metabolic control in AAs with poorly controlled T2DM. The long-term goal of the project is to identify effective strategies to improve metabolic control and hence reduce diabetes complication and mortality rates in AAs with T2DM.

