### **Primary Objective**

To test the efficacy of three financial incentive structures in combination with technology intensified diabetes education and skills training intervention on HbA1c levels in AAs with T2DM.

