## **RESEARCH DESIGN AND METHODS**

**Study Overview.** The overarching aim of this proposal is test the efficacy of three financial incentive structures in combination with technology intensified diabetes education and skills training intervention on blood pressure and quality of life in AAs with T2DM. 60 AAs with T2DM will be randomized to three groups with varying frequency of financial incentives: 1) High Frequency: financial incentives for weekly uploads plus average glucose, incentives for weekly attendance to educational sessions, and incentives at the end of the study for meeting HbA1c goals 2) Moderate Frequency: financial incentives for weekly uploads plus average glucose, and incentives at the end of the study for meeting HbA1c goals, and 3) Low Frequency: financial incentives at the end of the study for meeting HbA1c goals.

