**Covariates: Demographics:** Previously validated items from the National Health Interview Survey will be used to capture demographic characteristics. **Social support:** The Medical Outcomes Study (MOS) Social Support Survey (Sherbourne & Stewart 1991) will be used to measure social support. The total scale ( $\alpha=0.97$ ) has high internal consistency, good criterion and discriminant validity, and one-year test-retest reliability (0.72 to 0.76). **Health Literacy:** This will be assessed by the abbreviated version of the Test of Functional Health Literacy in Adults (S-TOFHLA) (Baker et al, 1999). The S-TOFHLA has a 0.80 correlation with the Rapid Estimate of Adult Literacy in Medicine (REALM). **Depression:** The PHQ-9 is a brief questionnaire that scores each of the 9 DSM-IV criteria for depression as "0" (not at all) to "3" (nearly every day). PHQ-9 score  $> \text{or} = 10$  have a sensitivity of 88% and a specificity of 88% for major depression (Kroenke 2001). **Medical Comorbidity:** The

patient's history of medical comorbidity will be documented using Chronic Health Conditions previously validated items from the Behavioral Risk Factor Surveillance System (BRFSS, 2010). **Diabetes Fatalism:** This will be measured with the 12-item Diabetes Fatalism Scales (DFS) (Egede 2009), a valid and reliable measure of diabetes fatalism ( $\alpha=.804$ ) that is associated with self-care problems, poor glycemic control, and decreased quality of life.

**Patient Randomization:** A permuted block randomization method will be used to assign subjects to one of the three intervention groups 1) High Frequency, 2) Moderate Frequency, and 3) Low Frequency. Block size will be varied to minimize the likelihood that the blind will be broken. The randomization will be stratified by baseline HbA1c levels (8-10% vs. >10%). Using REDCap, RAs will collect eligibility information and enter the information into the study database via the secured study website. Once eligibility is confirmed, the computer will generate the intervention assignment based on the pre-programmed randomization scheme. All subjects who are randomized will be entered into the study database and analyzed according to CONSORT guidelines (Altman 2001).

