### **3. POTENTIAL BENEFITS OF THE PROPOSED RESEARCH TO THE SUBJECTS AND OTHERS**

The intervention is expected to benefit patients, by increasing their knowledge of diabetes, activating and empowering them to better care for their diabetes, improving blood glucose and blood pressure control, and reducing their risk of developing complications of diabetes. Patients in the usual care group will benefit by increasing their general health knowledge.

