### **4. IMPORTANCE OF KNOWLEDGE TO BE GAINED**

The proposed study is innovative for a variety of reasons. First, behavioral economics is an emerging area of research that is not well tested in diabetes. Even though it is generally accepted that financial incentives can act as motivators to effect change in personal health behaviors (Sutherland 2008), few studies have assessed the effect of financial incentives on improving metabolic outcomes in T2DM. More importantly, there is little data on the effectiveness of financial incentives as motivators of behavior change in AAs. Second, the culturally-tailored education and skills training intervention proposed in this study is innovative because it targets patient level factors for which there is strong evidence of differences between AAs and Whites with T2DM (i.e. diabetes knowledge, self-management skills, empowerment, and fatalism/perceived control) (Egede 2005, Egede 2004, Nwasuruba 2007, Anderson 1995, Egede 2010). In addition, the intervention focuses on four key behaviors (physical activity, diet, medication adherence, and self-monitoring of blood glucose); maintains adequate dose and intensity of the intervention by delivering the intervention weekly for 12 weeks. Third, there are no large RCTs that have examined whether financial incentives augmented telephone-delivered diabetes education and skills training intervention will lead to greater improvements in metabolic control compared to usual care. Finally, the exploratory analyses will enable us to examine the effect of financial incentives augmented education and skills intervention on self-care behaviors and the mediation analysis will allow us to examine the contribution of self-care behaviors to improvements in metabolic control in African Americans with poorly controlled type 2 diabetes. With this approach, we can explore further targets for intervention in high risk African Americans with poorly controlled diabetes.

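### The stated aim is efficacy against usual care, but all 60 patients are randomised to incentive-plus-education arms, so that contrast cannot be estimated

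*Protocol*

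**What the plan says.** The protocol describes its comparison in two ways.

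- **With usual care.** Specific Aims opens its proposal with "We propose a pilot randomized controlled study to test the efficacy of financial incentives augmented telephone-delivered diabetes education" and skills training, and completes the sentence with "compared to usual care in improving metabolic control in AAs with poorly controlled T2DM". The Potential Benefits section says "Patients in the usual care group will benefit by increasing their general health knowledge".
- **Without usual care.** The Primary Objective is "To test the efficacy of three financial incentive structures in combination with technology intensified diabetes education and skills training intervention on HbA1c levels"; it names no comparator. The Study Overview says "60 AAs with T2DM will be randomized to three groups with varying frequency of financial incentives", and Human Subjects Involvement repeats this. Patient Randomization will "assign subjects to one of the three intervention groups 1) High Frequency, 2) Moderate Frequency, and 3) Low Frequency".

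The intervention description gives the weekly telephone education to subjects without limiting it to any arm. The Financial Incentives Component offers each of the three groups up to $300.

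The Data Analysis section, for the primary and secondary aims alike, specifies paired t-tests of change from baseline to 3 months within each arm. Sample Size and Power is likewise stated for change within each group.

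The Study Overview and Human Subjects Involvement also give an overarching aim in terms of blood pressure and quality of life, whereas the Primary Objective and the primary outcome are HbA1c.

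**The concern.** The comparator in the aim fixes what the trial may conclude. A reader of Specific Aims will expect a randomised estimate of the package against usual care. The only tests planned are changes from baseline in treated patients, so a significant fall in one or more arms could be read as the promised efficacy result.

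A change from baseline without a concurrent control mixes the intervention effect with everything else that moves HbA1c over 3 months. That includes regression to the mean, because patients enter on a screening HbA1c of at least 8%.

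The benefit sentence matters separately. It sits in the human-subjects section and describes to its readers a group of patients, and a benefit to them, that the design does not contain.

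**Working it through.** The main point is structural, so the first step sets the texts side by side. The arithmetic afterwards concerns only what the randomised comparison that does exist can deliver.

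**1. Which contrasts can be estimated**

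| Arm | n | Education | Incentive |
|---|---|---|---|
| Low Frequency | 20 | yes | up to $300 |
| Moderate Frequency | 20 | yes | up to $300 |
| High Frequency | 20 | yes | up to $300 |
| Usual care | 0 | – | – |
| Education only | 0 | – | – |

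- Package versus usual care needs a usual-care arm: 0 of 60 patients.
- Incentives versus none, with education held constant, needs an education-only arm: 0 of 60 patients.
- One incentive frequency versus another can be estimated, but the protocol specifies no between-arm test.

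**2. The protocol's own power figure**

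Sample Size and Power gives 85% power with 18 per group for a 1.0 SD effect, two-sided alpha 0.05, intra-class correlation at most 0.5, HbA1c SD 1.5, inflated by 10% to 20 per group.

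- Two-sample comparison, normal approximation: power = Φ(1.0 × √(18/2) − 1.96) = Φ(1.04) = 85.1%. The exact t gives 83.0%. Inflation: 18/0.9 = 20. This reproduces the stated figure.
- The planned paired test has SD of change = SD × √(2(1 − 0.5)) = 1.0 SD. At n = 18 the exact t gives 97.9% for a 1.0 SD change. For 1.0 point with SD 1.5 it gives 76.0% (80.7% at n = 20).

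So 85% matches a between-group calculation at 1.0 SD, while the text applies it to within-group change. Neither reading involves usual care.

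**3. What 20 per arm gives for a comparison between two incentive arms**

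Inputs: difference 1.0 point (the protocol's raw figure) and SD of change 1.5 × √(2(1 − 0.5)) = 1.5. The correlation of 0.5 is the protocol's upper limit and is an assumption here.

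- Normal approximation: Φ((1.0/1.5) × √(20/2) − 1.96) = Φ(0.15) = 55.9%. Exact t: **53.8%, about 54%**.
- 95% confidence interval half-width: 2.024 × 1.5 × √(2/20) = 0.96 points.
- If 3-month HbA1c is adjusted for baseline, the residual SD at correlation 0.5 is 1.5 × √(1 − 0.5²) = 1.30. Power rises to about 66% and the half-width falls to about 0.83 points.
- With three pairwise comparisons at 0.05/3 each, the change-score power is about 36%.

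**4. What a usual-care comparison would take**

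On the same assumptions (1.0 point, SD of change 1.5), 85% power for one comparison needs n = 2 × (1.96 + 1.036)² × 1.5² / 1.0² = 40.4, so 41 per arm (42 by exact t), or 46 to 47 after 10% inflation. Splitting the present 60 into four arms of 15 would give about 42% by exact t. A usual-care arm is therefore not a small addition to this design.

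**The case against.** The strongest defence is that the usual-care wording is a residue in narrative text. The objectives, incentive structure, randomisation, sample size and analysis all describe a three-arm trial, and no test or sample size depends on usual care. That stands, and it limits the point: a reader might infer that the whole trial is built on a usual-care comparison, but the operative sections do not support that. It does not remove the error, because the sentence that says what the study is names a comparator that nobody is randomised to.

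Three further readings are tempting and are not supported.

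- **The usual-care sentence under Importance of Knowledge to be Gained.** A reader might take it as a second promise of this comparison. It says that large trials of that question are lacking. It describes a gap in the literature and can stay.
- **The mediation sentence in the same section.** It says "the mediation analysis will allow us to examine the contribution of self-care behaviors to improvements in metabolic control", and the protocol's analysis section contains no such analysis. That detail may be left to a statistical analysis plan, which is not at hand. Nor is mediation shown to be impossible, since the three randomised arms do provide contrasts.
- **A number for the fall in HbA1c expected without any effect.** The documents give no source-population mean and no firm repeat-measure correlation, so any figure would rest on added assumptions. The point does not need one.

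It is also fair to object that rewording the primary objective alone would do harm: an objective about differences between structures would have no planned test, because power and analysis concern within-arm change only. That is correct, and the fix has to deal with it.

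**Conclusion.** The point holds in limited form. The aim and the benefit statement describe a usual-care comparison and a usual-care group; the design has neither. With 0 of 60 patients in a usual-care or education-only arm, neither the package against usual care nor incentives against none can be estimated, and the planned paired tests cannot carry such a claim. This conclusion rests on the text alone and needs no numerical assumption.

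The randomised design can support comparisons among incentive frequencies, with modest power: about 54% for 1.0 point at 20 per arm on change scores. That figure assumes an SD of change of 1.5. A correlation below 0.5 would make the SD of change larger and the power lower. The correction should be made because it governs what may be concluded, and it is cheap.

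**What to change.** 1. **Specific Aims:** replace the usual-care comparator with a comparison among the three incentive frequencies.
2. **Potential Benefits:** delete the sentence about the usual-care group.
3. **Specific Aims or Study Overview:** state that the trial does not estimate the effect of the package against usual care, or of incentives against none.
4. **Primary Objective, if reworded to differences between the structures:** in the same amendment, add to the primary analysis a between-arm comparison of 3-month HbA1c adjusted for baseline. Report within-arm change as descriptive. In Sample Size and Power, give the between-arm precision or power for 20 per arm: about 54% for 1.0 point on change scores with SD 1.5, and higher with baseline adjustment if the correlation is near 0.5.
5. **Study Overview and Human Subjects Involvement:** align the overarching aim, now blood pressure and quality of life, with the HbA1c primary objective.

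The cost is a narrower claim, a little more analysis and a less favourable power statement. No extra patients or visits are needed. If the sponsor does want the usual-care question answered, that needs a randomised usual-care arm, a between-group analysis and a new sample size, on the scale shown in the working.

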### **Primary Objective**

To test the efficacy of three financial incentive structures in combination with technology intensified diabetes education and skills training intervention on HbA1c levels in AAs with T2DM.

### **Secondary Objectives**

1. To test the efficacy of three financial incentive structures in combination with technology intensified diabetes education and skills training intervention on blood pressure and quality of life in AAs with T2DM.
2. To test the efficacy of three financial incentive structures in combination with technology intensified diabetes education and skills training intervention on diabetes knowledge and self-care behaviors (medication adherence, diet, exercise, and self-monitoring of blood glucose).

## **RESEARCH DESIGN AND METHODS**

**Study Overview.** The overarching aim of this proposal is test the efficacy of three financial incentive structures in combination with technology intensified diabetes education and skills training intervention on blood pressure and quality of life in AAs with T2DM. 60 AAs with T2DM will be randomized to three groups with varying frequency of financial incentives: 1) High Frequency: financial incentives for weekly uploads plus average glucose, incentives for weekly attendance to educational sessions, and incentives at the end of the study for meeting HbA1c goals 2) Moderate Frequency: financial incentives for weekly uploads plus average glucose, and incentives at the end of the study for meeting HbA1c goals, and 3) Low Frequency: financial incentives at the end of the study for meeting HbA1c goals.

### **Study Population & Recruitment Plan**

Study clinics: The study sites for this study are MUSC general medicine, endocrine, family medicine, and community primary care clinics. The investigative team has access to patients in these clinics and letters of support from key physician collaborators in each of these clinics are attached.

Recruitment Strategy: We will use two complementary approaches to identify eligible study subjects. The first method will consist of systematic identification of AA patients with T2DM. After obtaining IRB approval for a partial waiver of HIPAA, we will use clinic-billing records over the previous 12-month period to identify AA subjects with ICD-9 codes consistent with a diagnosis of T2DM. The physicians of eligible patients will be notified of their patients' potential eligibility and asked permission to enroll their patients in this study. The

second method will consist of referrals from physicians, other clinic staff such as nurses, or patients themselves in response to recruitment flyers for the study.

**Participant Payment:** Participants will receive \$25 each for completion of baseline and 3 month assessments for a total payment of \$50.

**Patient eligibility criteria:** The study inclusion and exclusion criteria are as follows

**Inclusion Criteria:** 1) Age  $\geq 21$  years; 2) Clinical diagnosis of T2DM and HbA1c  $\geq 8\%$  at the screening visit; 3) Self-identified as AA; 4) Subject must be taking an oral medication or insulin for diabetes to be able to assess medication adherence; 5) Subjects must be able to communicate in English; 6) Subjects must have access to a telephone (landline or cell phone) and/or ethernet for the study period; and 7) Subjects must be willing to use the FORA monitoring system for 3 months.

**Exclusion Criteria:** 1) Mental confusion on interview suggesting significant dementia; 2) Participation in other diabetes clinical trials; 3) Alcohol or drug abuse/dependency; 4) Active psychosis or acute mental disorder; and 5) Life expectancy  $< 12$  months.

### **Description of the Financial Incentive augmented Telephone-Delivered Diabetes Education and Skills Training Intervention:**

The financial incentives augmented telephone-delivered education and skills training intervention is comprised of two components: financial incentives and telephone-delivered education and skills training. Details of each component are provided below.

1. **The Telephone-Delivered Diabetes Education and Skills Training Component.** Subjects will receive weekly telephone-delivered diabetes knowledge/information, patient activation, patient empowerment, and behavioral skills training delivered via telephone. The intervention will be delivered by telephone once a week for 12 weeks with each session lasting ~30 minutes.

#### 2. **The Financial Incentives Component.**

**Structure of Incentives:** The reward system is structured as follows:

- Low Frequency Financial Incentive – Group 1: the low frequency incentive structure will receive a reward for absolute percentage drops in HbA1c from baseline at 3-month follow-up, up to \$300.
  - After 3 months, if their HbA1c has dropped 2% from baseline, or absolute HbA1c is 7%, they will receive a reward of \$300, for a 1% drop, or an absolute HbA1c between 7 and 8 they will receive a reward of \$150.
- Moderate Frequency Financial Incentive – Group 2: the moderate frequency incentive structure will receive a reward or uploading glucose measurements, and absolute percentage drops in HbA1c from baseline at 3-month follow-up, up to \$300.
  - Each week participants in Group B can receive up to \$10 for uploading glucose measurements and having good glucose control throughout the week. For each day they upload at least one glucose measurement, they will receive \$1 (up to \$7 at the end of the week). If they upload measurements every day of the week and their average glucose measurements at the end of the week are 150 or below they will receive an additional \$3. Up to \$10 per week for 3-months.
  - After 3 months, if their HbA1c has dropped 2% from baseline, or absolute HbA1c is 7%, they will receive a reward of \$170, for a 1% drop, or an absolute HbA1c between 7 and 8 they will receive a reward of \$85.
- High Frequency Financial Incentive – Group 3: the high frequency incentive structure will receive a reward or uploading glucose measurements, attending educational sessions, and absolute percentage drops in HbA1c from baseline at 3-month follow-up, up to \$300.
  - Each week participants in Group A can receive up to \$10 for uploading glucose measurements and having good glucose control throughout the week. For each day they upload at least one glucose measurement, they will receive \$1 (up to \$7 at the end of the week). If they upload measurements every day of the week and their average glucose measurements at the end of the week are 150 or below they will receive an additional \$3. Up to \$10 per week for 3-months.
  - Participants can also earn \$5 each week if they attend the educational session. Educational sessions will last for 8 weeks, so they can receive up to \$5 per week for 8 weeks.
  - After 3 months, if their HbA1c has dropped 2% from baseline, or absolute HbA1c is 7%, they will receive a reward of \$130, for a 1% drop, or an absolute HbA1c between 7 and 8 they will

receive a reward of \$65.

Thus, the maximum reward for each subject will be \$300 over the 3 months of intervention and follow up.

### **Data Collection Strategy**

**Personnel:** Two half-time masters-level trained diabetes educators (DEs) will deliver the interventions; one full-time research assistant (RA) will conduct screening, consent, enrollment procedures, and questionnaire administration; a half-time data entry clerk (DC) will be responsible for data entry; and a part-time masters-level statistician will be responsible for data management (DM). Each potentially eligible patient will be asked to report for a screening visit. At this visit, the following will be collected: basic demographic information, screening information, and a blood sample for a screening hemoglobin A1c (HbA1c) value. Basic demographic information will be collected to compare those screened to those randomized. Individuals who have a screening HbA1c of  $\geq 8$  will be asked to return within two weeks for a baseline visit. At the baseline visit, a full battery of questionnaires will be administered, and individuals will be randomized. All individuals randomized will have follow-up visits at 3 months, where survey questionnaires will be administered, and blood collected for HbA1c. Blood pressure will also be measured at the baseline and 3 months follow-up visit.

**Primary Outcome Measure: HbA1c:** About 10cc of blood will be drawn by trained phlebotomists and sent to the lab for HbA1c.

**Secondary Outcome Measures: Blood Pressure:** Blood pressure readings will be obtained using automated BP monitors (OMRON IntelliSense™ HEM-907XL). The device will be programmed to take 3 readings at 2 minute intervals, and give an average of the 3 BP readings. **Resource Utilization & Cost:** Previously validated questions on resource utilization will be administered. The questionnaires are 1 page long and capture information on hospitalizations, physician/professional visits, and medications. **Quality of Life:** The SF-12 (Ware 1996) is a valid and reliable instrument to measure functional status. The SF-12 items reproduce at least 90% of the variance in PCS-36 and MCS-36 scores.

**Process/Behavioral Measures: Information:** This will be measured by the 24-item Diabetes Knowledge Questionnaire (DKQ) (Garcia et al, 2001), which has reliability coefficient of 0.78, showed sensitivity to a diabetes knowledge intervention, and has been tested in an ethnic minority group. **Motivation:** This will be measured by the 8-item Diabetes Empowerment Scale-Short Form (DES-SF), which has a Cronbach's alpha of 0.85 (Anderson et al., 2003). **Self-Efficacy:** This will be measured by the 8-item perceived diabetes self-management scale (PDSMS) (Wallston et al., 2007), which has Cronbach's alpha of 0.83 indicating internal consistency. **Behavioral Skills:** This will be assessed with the Summary of Diabetes Self-Care Activities (SDSCA) scale (Toobert 2000), a brief, validated self-report questionnaire of diabetes self-care. **Treatment Credibility:** This will be assessed using a modified treatment credibility scale developed by Borkovec and Nau, but modified for diabetes intervention research (Egede 2010). **Delay Discounting:** This will be measured using the 10-item self-report Quick Delay Questionnaire (QDQ) developed to test two factors: 1) delay discounting and 2) delay aversion. Responses and attitudes toward delay activities and situations relevant to every day adult life are assessed. Individual respond on a five-point Likert scale with a score of one representing, "very like me", and five representing, "not like me at all". Test-retest for the two factors are  $r = 0.80$  for delay discounting and  $r = 0.81$  for delay aversion. Internal consistency is satisfactory for both factors (delay discounting— $\alpha = 0.68$ ; delay aversion— $\alpha = 0.77$ ) (Clare et al., 2010).

**Covariates: Demographics:** Previously validated items from the National Health Interview Survey will be used to capture demographic characteristics. **Social support:** The Medical Outcomes Study (MOS) Social Support Survey (Sherbourne & Stewart 1991) will be used to measure social support. The total scale ( $\alpha=0.97$ ) has high internal consistency, good criterion and discriminant validity, and one-year test-retest reliability (0.72 to 0.76). **Health Literacy:** This will be assessed by the abbreviated version of the Test of Functional Health Literacy in Adults (S-TOFHLA) (Baker et al, 1999). The S-TOFHLA has a 0.80 correlation with the Rapid Estimate of Adult Literacy in Medicine (REALM). **Depression:** The PHQ-9 is a brief questionnaire that scores each of the 9 DSM-IV criteria for depression as "0" (not at all) to "3" (nearly every day). PHQ-9 score  $> \text{or} = 10$  have a sensitivity of 88% and a specificity of 88% for major depression (Kroenke 2001). **Medical Comorbidity:** The

patient's history of medical comorbidity will be documented using Chronic Health Conditions previously validated items from the Behavioral Risk Factor Surveillance System (BRFSS, 2010). **Diabetes Fatalism:** This will be measured with the 12-item Diabetes Fatalism Scales (DFS) (Egede 2009), a valid and reliable measure of diabetes fatalism ( $\alpha=.804$ ) that is associated with self-care problems, poor glycemic control, and decreased quality of life.

**Patient Randomization:** A permuted block randomization method will be used to assign subjects to one of the three intervention groups 1) High Frequency, 2) Moderate Frequency, and 3) Low Frequency. Block size will be varied to minimize the likelihood that the blind will be broken. The randomization will be stratified by baseline HbA1c levels (8-10% vs. >10%). Using REDCap, RAs will collect eligibility information and enter the information into the study database via the secured study website. Once eligibility is confirmed, the computer will generate the intervention assignment based on the pre-programmed randomization scheme. All subjects who are randomized will be entered into the study database and analyzed according to CONSORT guidelines (Altman 2001).

**Sample Size and Power.** For the primary/secondary efficacy outcomes, HbA1c (Primary) and BP/QOL (Secondary), with 18 subjects randomized to each of the three intervention groups, we will have 85% power to detect at least a 1.0 standardized effect size (difference in within group means in sd units). This calculation assumes that the primary/secondary efficacy outcomes are measured at 2 time points (baseline and 3-months); the intra-class correlation for repeated observations is no greater than 0.5; level of significance ( $\alpha$ ) =0.05, two-tailed test. Assuming that HbA1c measurements have a standard deviation of approximately 1.5 based on our pilot studies, the study has 85% power to detect a difference of 1.0 percentage points (raw units) change in HbA1c within each of the three comparisons groups. Analyses for continuous secondary/exploratory outcomes (behavioral and process variables) also have 85% power to detect a standardized effect size of 1.0sd. To account for the "fraction of missing" information that must be imputed in the ITT sample and the dilution effect of ITT analyses (Hsieh et al., 2003) the sample size is inflated by 10% to achieve a final ITT sample size of 20 subjects randomized to each treatment group (N=60).

